#### Covariates

##### Sociodemographic Characteristics

Participants will be asked questions about their age, sex, postcode, ethnicity, education level, employment and income status, relationship status, living arrangements, and food security at 3, 6, and 12 months.

##### Self-Reported Physical Activity, Sitting Time, and Sleep

Physical activity (PA) and sitting time during the previous 7 days will be self-reported using the 7-item Godin Leisure-Time Exercise (frequency and duration of time in light/moderate/vigorous PA) [42] and the Marshall Sitting Time Questionnaire, respectively [43]. The Epworth Sleepiness Scale will be used to measure self-reported sleep [44]. This 8-item scale measures the general level of daytime sleepiness or average sleep propensity in daily life [44].

##### Smoking

Two items will be used to measure smoking: (1) Do you currently smoke any tobacco products? and (2) Would you have smoked 100 or more cigarettes or equivalent tobacco in your life? [45]. Moreover, 7-day abstinence will be measured at follow-up: “Have you smoked at least part of a cigarette in the last 7 days?” [46].

##### Depression, Anxiety, and Stress

Participants will complete the 21-item Depression, Anxiety and Stress Scale, which is a set of 3 self-report scales designed to measure the emotional states of depression, anxiety, and stress [47]. Each of the 21 items in the scale asks participants to report how much each item applied to them over the previous week using 4 responses (*never*, *sometimes*, *often*, or *almost always*) [47]. For example, “I found it hard to wind down.”

##### Social Desirability and Approval

Social desirability and approval have emerged as sources of bias in self-reporting of dietary intake [48]. Social desirability will be measured using the 13-item Marlowe-Crowne Social Desirability Scale [49] in which participants are prompted to answer true or false to a number of statements concerning personal attitudes and traits [49]. The Martin-Larsen Approval Motivation Scale, a 20-item 5-point Likert scale, will be used to measure social approval [50].

##### Social Influences on Food Intake

The Social Eating Scale will be used to measure influences such as culture, family, or peers on food intake, requiring participants to select the appropriate response from 6 questions using a 5-point Likert scale [51].

#### Economic Measures

There is no basis for anticipating that health service utilization will vary between trial arms as a result of the interventions. As a consequence, health service engagement is assumed to be randomized, and the requirement to collect health service engagement or medication use is excluded. The additional costs relating to the intervention and implementation of the intervention, including materials, labor, and other expenditures, will be collected through project management and project team records. The economic analysis will use either the change in ARFS or AQoL-6D as the outcome of interest. If the change in either is not statistically significant, all consequence measures, primary and secondary, will be reported alongside the cost estimates.

#### Engagement

Engagement will be measured using usage statistics captured by the website. The outcomes will include completion of the HEQ (control group only), the number of log-ins to the website, clicks on resources and links, views of personalized dietary feedback, and views and completion of goal setting and tracking (intervention groups 1 and 2). In addition, for intervention Group 2, engagement will be measured by attendance at the brief video consultation.

#### Reach and Recruitment Success

The number of people who engage with the various online recruitment strategies will be measured by using Bitly links [52], and the number of people who access and engage with the website will be measured by using Google Analytics. Bitly links allow the creation of customized URLs, which track back to the Aim4Me website and allow tracking of engagement with various strategies. Recruitment success will be measured by the time to recruit per strata, representativeness of the sample, number of people who expressed interest, percentage of eligible participants, and the number of those who consented. As part of the baseline assessment questionnaires, eligible participants will be asked how they found out about the study to capture which recruitment strategies were most successful.

#### Retention

Retention will be assessed as the proportion of participants who complete the AES at 3, 6, and 12 months.

#### Satisfaction

Self-reported satisfaction with study components will be evaluated at 3, 6, and 12 months using a process evaluation developed by the research team. Group 1 will be asked about their satisfaction with the HEQ if it was completed. For groups 2 and 3, questions will cover the personalized dietary feedback report, resources on the Aim4Me website, goal setting and tracking, and overall intervention satisfaction. Intervention Group 3 will also self-report satisfaction with the video consultation with the APD.

#### Scheduled Reminders and Prize Draw

All groups in the study will receive scheduled email and text message reminders to prompt the completion of assessment questionnaires at each time point (baseline and 3, 6, and 12 months). Emails will be sent 3, 6, and 9 days following the commencement of each phase, and text messages will be sent on day 9. Follow-up phone calls may also be scheduled at follow-up time points to prompt the completion of questionnaires. As an incentive to complete questionnaires and to promote retention, participants will automatically be entered into a gift voucher prize draw. Each draw will have a 1 in 100 chance of a prize, with the value of the gift voucher increasing in value over time (from Aus $100 [US $66.10] and up to Aus $400 [US $264.40] at 12 months).

### Sample Size

The sample size calculation was based on detecting changes in the primary outcome of diet quality score (AFRS), with adequate power to assess differences in daily servings of fruit and vegetables. The study aims for a between-group increase in ARFS of 2.2 (baseline SD 9.6) and fruit and vegetables serves per day of 0.56 (baseline SD 2.4) compared with no change in the control group [53]. To detect this between-group AFRS difference with an alpha of .05 and 80% power, 300 participants per arm across 3 arms are required, totaling 900 participants. Given that we also wish to examine this effect a priori in male and female subgroups separately, we will require 900 participants of each gender or 1800 in total. To allow for 10% loss to follow-up at 3 months, 20% at 6 months, and 30% at 12 months, the study requires a total sample of 2570 (1285 males and females each).

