### Statistical Analysis

The outcome effects will first be evaluated using independent *t* tests, followed by repeated measures within-group changes in the ARFS diet quality score and modeling between-group changes over time using the generalized linear mixed model. The model will be fitted with ARFS at all follow-up points as the outcome variable, with fixed effects for group, time, baseline ARFS, and time by group interaction. Covariates, including PA, sleep, smoking, and social desirability, will be included in the statistical model as potential confounders. Statistical significance of the primary efficacy analysis will be based on Hochberg multiple testing procedures with a family-wise error rate for each time point held at 2.5%. The main analysis will use a generalized linear mixed model with the outcome at all time points and intention-to-treat principle. Sensitivity analyses will be conducted with the last observation carried forward, with multiple imputations, and for completers only. Analyses will be performed using SAS version 9.4 or later (SAS Institute Inc). All variables will be checked for plausibility and missing values. Data will be presented as mean (SD) for continuous and count variables.

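### The 80% power is computed for one unadjusted test at two-sided .05, not for the Hochberg rule at 2.5% that the analysis applies; the pooled comparison is safe, the sex-specific power is unsettled

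*Protocol article*

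**What the plan says.** All places are in the protocol article.

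- **Sample Size.** The target is a between-group ARFS difference of 2.2 with a baseline SD of 9.6. On that basis: "To detect this between-group AFRS difference with an alpha of .05 and 80% power, 300 participants per arm across 3 arms are required", which makes 900 in all. No multiplicity allowance is mentioned.
- **Sample Size, doubling.** "Given that we also wish to examine this effect a priori in male and female subgroups separately", the authors conclude that "we will require 900 participants of each gender or 1800 in total". Allowance for 30% loss at 12 months then gives 2570.
- **Statistical Analysis.** Significance of the primary efficacy analysis rests on "Hochberg multiple testing procedures with a family-wise error rate for each time point held at 2.5" per cent. The section does not say whether this rate is one- or two-sided, which group comparisons form the family, or whether the rule extends to the separate male and female analyses.
- **Statistical Analysis, model.** Baseline ARFS is a fixed effect in the mixed model. The sample size uses the raw baseline SD and gives no baseline/follow-up correlation.

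**The concern.** A power figure describes a particular test at a particular level. Here the level in the sample size (.05, one comparison) and the level in the analysis (2.5%, shared across comparisons by Hochberg) differ, and nothing in the article reconciles them.

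The figure matters because the whole recruitment target is built on it. The 300 per arm is doubled so that each sex has its own 300 per arm, and is then inflated for loss. If the sex-specific tests follow the stricter rule, the justification for half the sample promises more power than those tests have on the plan's own inputs. A null result in one sex could then be given more weight than it deserves.

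**Working it through.** **Inputs.** Difference 2.2, SD 9.6, power 80%, alpha .05, 300 per arm per sex and 30% loss at 12 months (Sample Size); 1:1:1 allocation (Randomization); Hochberg at 2.5% per time point (Statistical Analysis). The number of comparisons is not given, so two (each intervention group against control) and three (all pairs) are both shown.

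**1. Reproduce the plan.** n per arm = 2(z₁₋ₐ/₂ + z₀.₈)² × 9.6² / 2.2².

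- Two-sided .05: 2 × (1.960 + 0.842)² × 92.16 / 4.84 = 298.9, matching the stated 300.
- One-sided .05 gives 236 and does not match. One-sided .025 is the same level as two-sided .05.
- Recruitment: 1800 / 0.70 = 2571.4, matching 2570 to rounding. Completers per arm per sex at 12 months: 1285 × 0.70 / 3 = 299.8.

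The arithmetic is therefore sound, but it contains no multiplicity allowance.

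**2. Power at the fixed levels through which Hochberg steps**, reading 2.5% as two-sided. Power = Φ(2.2 / [9.6√(2/n)] − z₁₋ₐ/₂). For n = 300 the first term is 2.2 / 0.784 = 2.807.

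| Two-sided level | z | Power, n = 300 | Power, n = 600 | n per arm for 80% |
|---|---|---|---|---|
| .05 (as planned) | 1.960 | 80.1% | 97.8% | 299 |
| .025 (largest p value) | 2.241 | 71.4% | 95.8% | 362 |
| .0125 (strictest of 2) | 2.498 | 62.1% | 92.9% | 425 |
| .00833 (strictest of 3) | 2.638 | 56.7% | 90.8% | 462 |

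The last three rows bracket Hochberg power; they are not themselves the power of the procedure.

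**3. Power of the Hochberg procedure itself.** This was simulated with three independent arm means, so that the contrasts are correlated, SD 9.6, and 1,000,000 runs per scenario. Entries are the power for one true 2.2 contrast at 300 per arm, with two / three comparisons in the family.

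| True effects of the two interventions | 2.5% two-sided | 2.5% one-sided |
|---|---|---|
| 2.2 and 2.2 | 68% / 60% | 78% / 70% |
| 0 and 2.2 | 62% / 60% | 71% / 70% |
| 2.2 and 4.4 | 71% / 70% | 80% / 79% |

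The range is about 60-71% two-sided and 70-80% one-sided. At 600 per arm (both sexes pooled) the two-sided range is 93-96%.

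**4. Earlier time points.** The rule applies at each time point and less loss is assumed earlier. At 3 months about 1285 × 0.90 / 3 = 385 per arm per sex remain: power 82.6%, 75.2% and 70.6% at .025, .0125 and .00833. At 6 months about 342 remain: 77.5%, 69.1% and 64.0%.

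**5. Baseline adjustment.** With correlation r between baseline and follow-up ARFS (not given in the article, so an assumption), the residual SD is 9.6√(1 − r²). Power at n = 300:

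| r | .025 | .0125 | .00833 |
|---|---|---|---|
| 0.3 | 76% | 67% | 62% |
| 0.5 | 84% | 77% | 73% |
| 0.6 | 90% | 84% | 81% |
| 0.7 | 95% | 92% | 90% |

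For 80% power at n = 300 the residual SD must fall to 8.74, 8.07 or 7.74, which means r of about 0.41, 0.54 or 0.59 respectively.

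**The case against.** A reader might infer that the sex-specific comparisons definitely lack 80% power. The article does not support that, for three reasons.

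- **Scope.** The Hochberg rule is stated for the primary efficacy analysis. The sex analyses are described only as an a priori examination of the same effect. If they are tested at unadjusted two-sided .05, 80% stands. It is also true that the article gives no other significance rule for them.
- **Sidedness.** If 2.5% is one-sided, the base level equals the planning level, and only the Hochberg split costs power. That loss is smaller, and it nearly vanishes in the graded scenario. There, however, one intervention has an effect of 4.4, which the plan does not assume.
- **Baseline adjustment.** The planned model includes baseline ARFS, and a moderate correlation would recover the loss. But the sample size neither uses nor states a correlation, so this recovery cannot be credited to the plan as written.

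It can also be said that sidedness, the family and the subgroup rules belong in a full protocol or analysis plan that is not shown. That is fair for those details, and their absence alone is no fault. What remains is that two levels the article does state, .05 and 2.5% family-wise, do not match.

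A second tempting reading is that the trial's main comparison is underpowered. It is not: even at the strictest step of three, the pooled sample has 90.8% power.

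**Conclusion.** The mismatch holds. The 300 per arm and the 80% are correct for one unadjusted comparison at two-sided .05, and that is not the test the analysis section describes.

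The consequence is confined to the sex-specific analyses and is conditional. At 12 months, with a difference of 2.2, SD 9.6, 300 completers per arm and no baseline gain, the shortfall from 80% is about 9 to 20 percentage points if the Hochberg rule covers these analyses two-sided, and about 0 to 10 points if it covers them one-sided. There is none if they are tested at unadjusted two-sided .05, and it could disappear with a sufficient baseline correlation.

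Severity is moderate: a power figure on which the recruitment target depends should match its test, but the pooled primary comparison keeps more than 90%.

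**What to change.** Revise the Sample Size paragraph so that power is stated for the rule in the Statistical Analysis section:

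1. Say whether 2.5% is one- or two-sided, which group comparisons form the Hochberg family, and whether the rule covers the male and female analyses. If it does not, state the level at which those are tested.
2. Give separate power figures for the pooled comparison (600 completers per arm) and the sex-specific comparisons (300 per arm). Compute them for the Hochberg procedure itself, not only at its fixed step levels.
3. Since the main model adjusts for baseline ARFS, use the residual SD 9.6√(1 − r²) with a stated and justified r, and show power over a range of r.

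This costs a paragraph and a short calculation, with no extra participants. The downside is that the published sex-specific power may become less favourable than 80%.

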### Statistical Analysis

The outcome effects will first be evaluated using independent *t* tests, followed by repeated measures within-group changes in the ARFS diet quality score and modeling between-group changes over time using the generalized linear mixed model. The model will be fitted with ARFS at all follow-up points as the outcome variable, with fixed effects for group, time, baseline ARFS, and time by group interaction. Covariates, including PA, sleep, smoking, and social desirability, will be included in the statistical model as potential confounders. Statistical significance of the primary efficacy analysis will be based on Hochberg multiple testing procedures with a family-wise error rate for each time point held at 2.5%. The main analysis will use a generalized linear mixed model with the outcome at all time points and intention-to-treat principle. Sensitivity analyses will be conducted with the last observation carried forward, with multiple imputations, and for completers only. Analyses will be performed using SAS version 9.4 or later (SAS Institute Inc). All variables will be checked for plausibility and missing values. Data will be presented as mean (SD) for continuous and count variables.

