### Randomization

Eligible participants will be randomly allocated (1:1:1) to a control group or 1 of 2 intervention groups. Randomization will occur in permuted blocks using random blocks of varying size and be stratified by postcode location (using the Monash Modified Model) [25], sex, and BMI (18.5-24.9 kg/m^2^ vs ≥25 kg/m^2^). Randomization will be coded by an independent statistician who will provide the coding to the software developers to program the web-based environment. The research team will remain blinded to the randomization code.

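### Randomization is stratified by location, sex and BMI category, but the primary model names none of them; its standard errors may be modestly conservative, and adding the factors costs almost nothing.

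*Protocol article*

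**What the plan says.** On design, the Randomization section states "Eligible participants will be randomly allocated (1:1:1) to a control group or 1 of 2 intervention groups". It continues "Randomization will occur in permuted blocks using random blocks of varying size", with strata formed by location, sex and two BMI categories.

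On analysis, the Statistical Analysis section begins with an unadjusted step: "The outcome effects will first be evaluated using independent *t* tests". It then fits a mixed model to ARFS at the follow-up points "with fixed effects for group, time, baseline ARFS, and time by group interaction", and adds: "Covariates, including PA, sleep, smoking, and social desirability, will be included in the statistical model as potential confounders". A later sentence reads: "The main analysis will use a generalized linear mixed model with the outcome at all time points and intention-to-treat principle". Nowhere does the article say that the stratification factors will enter the analysis.

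The Sample Size section plans on a "between-group increase in ARFS of 2.2 (baseline SD 9.6"), 80% power, alpha .05 and 300 participants per arm. It doubles this to 1800 so that each sex can be examined separately, and enlarges it to 2570 for 30% loss by 12 months.

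**The concern.** Blocking within strata removes most chance imbalance between arms on the stratification factors. If those factors are prognostic, the true sampling variance of the treatment contrast falls. A model that leaves them out still counts the between-stratum variation as residual noise. Its reported standard error then describes a less efficient design than the one that was run, so intervals are too wide and tests conservative.

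This is more than detail that an article leaves to a later document. The section lists its fixed effects and names four covariates, yet passes over the three variables that the trial chose to balance. At stake is some precision, chiefly in the male and female analyses, each planned at only 80% power. The validity of the comparison is not in question.

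**Working it through.** **1. Reproduce the plan's figures.** Inputs from the Sample Size section: difference 2.2, SD 9.6, alpha .05 (two-sided assumed), power 80%.

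n per arm = 2 × (1.960 + 0.842)² × 9.6² / 2.2² = 298.9, so 299 against the stated 300. Power at 300 per arm is 80.1%. Loss to follow-up: 1800 / 0.70 = 2571.4, so 2572 against the stated 2570. Both reproduce, and neither depends on the strata.

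**2. Formulas.** Let R² be the share of ARFS variance remaining after baseline ARFS that location, sex and BMI category explain. The documents do not give it; I take 0 to 10% as an assumption. With arms balanced within strata:

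- SE reported without the strata: S = 9.6 × √(2/n)
- true SE, and SE reported with the strata: T = S × √(1 − R²)
- overstatement of the SE: 1/√(1 − R²)
- type I error without the strata: 2 × [1 − Φ(1.96 × S/T)]
- power without the strata: Φ((2.2 − 1.96 × S)/T)
- power with the strata: Φ(2.2/T − 1.96)

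**3. Results at 300 per arm (one sex), S = 9.6 × √(2/300) = 0.784.**

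| R² | T | SE too wide by | Type I error without strata | Power without | Power with | Gain (points) |
|---|---|---|---|---|---|---|
| 0 | 0.784 | 0 | 5.0% | 80.1% | 80.1% | 0 |
| 2% | 0.776 | 1.0% | 4.8% | 80.4% | 80.9% | 0.5 |
| 5% | 0.764 | 2.6% | 4.4% | 80.8% | 82.1% | 1.4 |
| 10% | 0.744 | 5.4% | 3.9% | 81.4% | 84.1% | 2.7 |

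Gains are taken from unrounded powers.

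**4. Results at 600 per arm (both sexes), S = 0.554.** At R² = 10%, power goes from 98.3% to 98.7%, a gain of 0.4 points.

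**5. Sensitivity.** The table uses 9.6 as the residual SD, as the plan does. If baseline ARFS correlates 0.5 with follow-up (assumption), the residual SD is 9.6 × √(1 − 0.25) = 8.31, and the gain at 300 per arm and R² = 10% falls to 1.6 points (91.1% to 92.7%). In the other direction, the Statistical Analysis section holds the family-wise rate at 2.5% per time point. With 2.241 in place of 1.96 and SD 9.6, the same case goes from 72.4% to 76.3%, or 3.9 points. The SE overstatement is the same in all these cases.

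**6. Simulation.** 4,000 trials per setting: 1800 participants, blocked 1:1:1 within strata, seven location categories assumed, baseline correlation 0.6 assumed. Mean reported SE without and with the strata:

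- R² = 0: 0.4435 and 0.4435
- R² = 2%: 0.4434 and 0.4390
- R² = 5%: 0.4436 and 0.4324
- R² = 10%: 0.4435 and 0.4207

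The last three ratios are 1.010, 1.026 and 1.054, matching the formula. Type I error without the strata was 4.0% at R² = 10%. At smaller R² it could not be told from 5%, given simulation error of about 0.35 points.

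**The case against.** The covariate sentence opens with the word *including*, so its list is formally open, and this is a condensed article whose full analysis plan is not shown. The strata are not excluded and may yet be added. That stands, and it softens the point. It does not remove it, because the section chose to name its terms and left these out.

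Baseline ARFS may already absorb most of any stable relation between sex, BMI or location and diet quality. That also stands, which is why the range must start at zero.

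A reader might infer more than the documents support:

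- **That the standard errors are too wide as a fact.** This holds only if the strata predict follow-up ARFS beyond baseline ARFS, and no figure is given.
- **That omitting the strata wastes about 50 to 285 of the 2570 participants.** That figure is 1/(1 − R²) at 2 to 10%, and it measures reported interval width. Under stratified blocks the unadjusted estimate already has the smaller true variance. In terms of power, the equivalent is 1.4 to 7.3% more participants at 300 per arm and 1.0 to 5.1% at 600.
- **That the SE overstatement is greatest within each sex.** Sex is constant there and explains nothing; only location and BMI can contribute. A given R² costs more power points in those analyses simply because they start near 80%.
- **That baseline ARFS is both outcome and covariate, giving a type I error of 8 to 10%.** The section explicitly fits the follow-up scores with baseline as a covariate. The later phrase about all time points is loose wording, and the list of time points that includes baseline (Scheduled Reminders and Prize Draw) concerns questionnaire reminders. The 8 to 10% also needs a random-intercept covariance, which the article does not state; one check with an unstructured covariance and correlation 0.4 gave 5.2% over 500 runs.

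**Conclusion.** The point holds as a modest matter of efficiency. The model as written does not reflect the stratified design. For an assumed residual R² of 0 to 10%, reported standard errors are 0 to 5.4% too wide. At the plan's own SD of 9.6 and two-sided alpha of .05, this costs 0 to about 2.7 points of power at 300 per arm and at most about 0.4 points at 600 per arm. Any error is in the conservative direction: the treatment estimate is unbiased and type I error is not inflated.

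These sizes rest on the assumed R², and on the arms staying close to balanced within strata among those analysed, which 30% loss by 12 months will loosen somewhat. The sentence on the outcome is a wording matter only. The change is worth making because it is nearly free; nothing in the sample size has to move.

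**What to change.** In the Statistical Analysis section, add sex, BMI category and location stratum, as used at randomization, to the fixed effects of the primary model. In the male and female analyses, add BMI category and location only. State in advance how sparse location categories will be pooled; that is the one small downside. In the sentence on the main analysis, replace *time points* with *follow-up points*, so that it matches the model already stated there.

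The cost is about two sentences of text. All three variables are held from randomization, so no new data are needed and the sample size is unchanged. The change should be made before outcome data are examined by arm.

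### The mixed model gives baseline ARFS a single slope across 3, 6 and 12 months; adding a baseline-by-time term is a cheap safeguard against a small, conditional bias at 12 months

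*Protocol article*

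**What the plan says.** All of this is in the protocol article, Methods.

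- **Outcome of the model (Statistical Analysis):** "The model will be fitted with ARFS at all follow-up points as the outcome variable".
- **Fixed effects (same section):** "with fixed effects for group, time, baseline ARFS, and time by group interaction". Group is allowed to act differently at each visit; baseline is not.
- **Other covariates (same section):** "Covariates, including PA, sleep, smoking, and social desirability, will be included in the statistical model as potential confounders".
- **Second description of the main analysis (same section):** "The main analysis will use a generalized linear mixed model with the outcome at all time points and intention-to-treat principle".
- **Error control (same section):** "Hochberg multiple testing procedures with a family-wise error rate for each time point held at 2.5" per cent. Each visit is therefore judged separately, and 12 months is not singled out as primary.
- **Expected loss (Sample Size):** "To allow for 10% loss to follow-up at 3 months, 20% at 6 months, and 30% at 12 months". Nothing is said on whether loss depends on baseline ARFS or differs by arm.

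**The concern.** With one baseline coefficient, the fitted slope is a compromise across visits, weighted towards the earlier ones, which keep more participants. If the relation between baseline and later diet quality weakens over the year, the compromise is too steep at 12 months. That does no harm to a between-arm contrast as long as the participants observed at 12 months have similar baseline ARFS in each arm. If they do not, the excess slope multiplied by the baseline gap goes into the treatment contrast.

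Both conditions are plausible here, though not documented. Participants in Groups 2 and 3 set goals from their dietary feedback and are prompted to revise them at 3 and 6 months, which could loosen the tie to baseline. The arms also differ greatly in what they receive: Group 1 completes the Australian Eating Survey without its feedback report, while Group 3 is offered a dietitian. The kind of participant who stays could therefore differ by arm. The contrast at risk is the one with the most planned loss, and it is tested in its own right.

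**Working it through.** **1. The plan's own figures.** Inputs from Sample Size: difference 2.2, SD 9.6, alpha 0.05 (taken as two-sided), power 80%.

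n per arm = 2 × (1.960 + 0.842)² × 9.6² / 2.2² ≈ 2 × 7.85 × 19.04 ≈ 299, against the stated 300. Doubling 900 for the two sexes gives 1800, and 1800 / 0.70 ≈ 2571, against the stated 2570. The figures reproduce. The formula takes no credit for baseline adjustment, so the choice of baseline term does not change the sample size.

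**2. Set-up of the check.** From the documents: SD 9.6, true effect 2.2, monotone loss of 10/20/30%, and 2570 / 3 ≈ 857 per arm. Assumed: baseline slopes at 3/6/12 months; residual correlation between visits of 0.3 or 0.6; log-odds of dropout per SD of baseline, by arm; unstructured covariance. Control was compared with one active arm. Each scenario used 40,000 simulated participants per arm, with standard errors (SE) rescaled to 857. Both models were fitted to the same data. The bias is the 12-month estimate from the one-slope model minus that from the model with baseline by time. The latter stays near the true 2.2 in all scenarios, within simulation noise.

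**3. Bias at 12 months (ARFS points; range over the two residual correlations).**

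| Slopes 3/6/12 months | Dropout dependence equal in both arms (0.5, 0.5) | One arm only (0, 0.5) | Opposite (−0.5, +0.5) | Strongly opposite (−1, +1) |
|---|---|---|---|---|
| 0.60/0.60/0.60 (constant) | 0.00 | −0.01 to 0.00 | 0.00 to 0.01 | −0.02 to −0.01 |
| 0.70/0.65/0.60 (moderate) | 0.01 | 0.09 to 0.11 | 0.19 to 0.20 | 0.36 to 0.37 |
| 0.70/0.60/0.50 (moderate) | −0.01 to 0.01 | 0.20 to 0.22 | 0.39 to 0.45 | 0.71 to 0.79 |
| 0.80/0.60/0.40 (extreme) | −0.01 to 0.03 | 0.45 to 0.50 | 0.90 to 1.00 | 1.52 to 1.73 |

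The first row and the equal-dependence column show that both conditions are needed. For the two moderate rows, with dependence in one arm or opposite at 0.5, the bias is 0.09 to 0.45: 0.09 / 2.2 ≈ 4% and 0.45 / 2.2 ≈ 20% of the target.

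**4. Hand check of the mechanism.** Bias ≈ (fitted slope − true 12-month slope) × baseline gap between the arms' 12-month responders.

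- Slopes 0.70/0.60/0.50, residual correlation 0.3, one arm only: fitted slope 0.637, gap 1.39. (0.637 − 0.50) × 1.39 ≈ 0.19; simulated 0.20.
- The same with opposite dependence: fitted slope 0.633, gap 2.61. 0.133 × 2.61 ≈ 0.35; simulated 0.39.

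The simulated values are a little larger because the model also uses the earlier visits through the residual correlation.

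**5. Precision.** Ratio of 12-month SEs, one-slope over baseline by time, with no dropout dependence: 1.000 with a constant slope, 1.003 to 1.016 in the moderate rows, and 1.06 to 1.08 in the extreme row. In the other direction, with a constant slope and strongly opposite dropout the ratio falls to 0.977, so the added term then costs about 2%.

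**6. Scale against the SE.** At 12 months about 857 × 0.70 ≈ 600 per arm remain. With a 12-month slope of 0.6, SE ≈ 9.6 × √(1 − 0.36) × √(2/600) ≈ 0.44, which agrees with the simulation. The moderate range runs from 0.09 / 0.44 ≈ 0.2 SE to 0.447 / 0.4675 ≈ 1.0 SE (0.4675 is the simulated one-slope SE in that scenario).

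**The case against.** **Neither condition is documented.** The article gives overall loss only, and no correlation between baseline and follow-up ARFS. This stands: the mechanism is certain, the size is not. The upper part of the moderate range is also demanding. Opposite dependence of 0.5 per SD leaves 12-month responders differing at baseline by about 2.6 to 2.8 points in those rows, more than the 2.2-point target. With dependence in one arm only, the gap is 1.3 to 1.4 points and the bias 0.1 to 0.2.

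**The model may be something else.** The second description of the main analysis could mean that baseline ARFS is itself an outcome. With an unstructured covariance, each visit would then have its own relation to baseline and the issue would vanish. That reading is possible, but it does not clearly override the sentence that makes follow-up ARFS the outcome and lists baseline as a fixed effect. A statistical analysis plan that is not shown may add the term. The point concerns the list that the article does state.

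**Multiple imputation is planned.** If every randomised participant contributes at 12 months, baseline is balanced by randomisation and a common slope does no between-arm harm, provided that the imputation model lets the baseline relation vary by visit. This is fair, but it is a sensitivity analysis and leaves the main result as it is.

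**A stronger reading to avoid.** A reader might infer that the 12-month result is biased as planned, with a badly inflated error rate. Correlations of 0.80/0.70/0.60 with opposite dropout of 0.5 per SD do give a bias of 0.54 points and 23% rejection at a nominal 5%. The documents support neither input, and the trial tests at a 2.5% family-wise level per visit, so 23% is not its error rate. Nor is differential dropout enough alone: with a constant slope the bias is about zero.

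**Conclusion.** The point holds as a low-severity matter of model specification. The stated fixed effects force one baseline slope on all three follow-up visits. If the slope changes over time and dropout depends on baseline ARFS differently by arm, the 12-month contrast is biased by roughly 0.1 to 0.45 points under moderate assumptions. If either condition is missing, there is essentially no bias. These sizes rest on assumed slopes, residual correlations, dropout models and covariance structure, none of which the article gives. A reader might also infer a general loss of precision, but that effect is small and disappears when the slope is constant. The case for acting is that the trial cannot rule out the two conditions in advance, each visit is tested separately, and the remedy costs almost nothing.

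**What to change.** Add a baseline ARFS by time interaction, with time as a factor, to the listed fixed effects, and estimate the group contrasts at 3, 6 and 12 months from that model. In the same sentence, confirm that the outcome is the three follow-up visits, so that the two descriptions of the main analysis agree.

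The cost is one sentence and 2 degrees of freedom, against 1800 or so participants expected at 12 months, with no new data and no change to the sample size. The one statistical downside is a standard error up to about 2% larger if the slope is in fact constant and dropout strongly differential. The article reports 1277 of 2570 randomised with data collection continuing, so at that stage the term could still be pre-specified before analysis.
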